#### 4.4.3 Follow up visits (Visit 3 and Visit 4)

Following steps will be carried out during the Visit 3 (1 month) and Visit 4 (2 month)

- Record AEs and SAEs since the previous visit.
- Perform pregnancy test & contraception review if applicable. If the pregnancy test is positive, then fill the EOS form and terminate the participant.
- Measure SBP, DBP and pulse (two BP readings will be taken with minimum of 3 min gap)
- Anthropometric measurements – Weight / WC / HC / mid arm circumference
- Review and record all medications being taken by the participant.
- Collect unused trial medication and review medication adherence.
- Issue new pack of treatment drug/placebo as per the initial allocation

#### 4.4.4 Follow up visit (Visit 5 – EOS)

At the end of the study

- Record AEs and SAEs since the previous visit.
- Measure SBP, DBP and pulse (two BP readings will be taken with minimum of 3 min gap)
- Anthropometric measurements – Weight / WC / HC / mid arm circumference
- Review and record all medications being taken by the participant.
- Collect unused trial medication and review medication adherence.
- Collect blood for investigations

- Record laboratory results (FBS, HbA1c, lipid profile, liver profile, serum creatinine, ACR, electrolytes, eGFR). Each test should be conducted by the same laboratory that conducted the investigations at the screening and/or baseline.
- Collect unused trial medication and review medication adherence.
- Any ongoing AE reported at the EOS will be followed up by the investigators until it is resolved.

## 4.5 Blinding

The investigators and participants will be remained blinded to the treatment allocations. The medication will be delivered in similar bottles and labels, each with its own sequence number. Bottles containing a monthly supply of either placebo or cinnamon capsule will be prepared according to the randomization sequence and supplied to the participants by the investigator or research assistants when they are randomized to the trial.

## 4.6 Data collection methods

### 4.6.1 Baseline data collection

Those who consent and are eligible will constitute the study sample (n=150 or 75 per arm). Domains of the baseline data collection form include socio-demographic information, vitals (SBP, DBP and pulse), anthropometric measures (Height, Weight, WC, HC and mid arm circumference) will be recorded. Fasting (12 hrs) blood samples (10 ml) will be collected to analyse total cholesterol, HDL, LDL, triglycerides, FBS, HbA1c, liver profile (ALT, AST, AP), and renal profile (Serum creatinine, eGFR, Electrolytes – Na, K, Cl), Urine sample (20 ml) will also be collected to analyse ACR. All individuals with elevated lipid levels will be advised by investigator on lifestyle modification including diet and physical activity.

#### 4.6.2 Follow up data collection

All participants will be requested to visit the clinic in one-month intervals for next three months and anthropometric measures, SBP, DBP and pulse will be recorded over a three months period post randomization. Any AEs since the last visit and all the medications being taken by the participants will be recorded. Unused medication (IMP) will be collected and the drug compliance will be determined. During visit 05, all the laboratory investigations carried out at the visit 1 will be repeated.

#### 4.7 Study duration

The study will be for a period of 3 months and the visits and the evaluations will be done as follows: screening (visit 1) and randomization (visit 2), 1 month (visit 3), 2 months (visit 4) and 3 months (visit 5) (Table 1).

*Table 1: Data collection*

| Timepoint                                          | Study period         |                        |               |               |               |
|----------------------------------------------------|----------------------|------------------------|---------------|---------------|---------------|
|                                                    | Screening
Visit 1 | Recruitment
Visit 2 | Visit 3       | Visit 4       | Visit 5       |
|                                                    | -7 days              | Day 0                  | Day
30(+5) | Day
60(+5) | Day
90(+5) |
| Enrollment                                  |                      |                        |               |               |               |
| Eligibility Screen                                 | X                    |                        |               |               |               |
| informed Consent                                   | X                    |                        |               |               |               |
| Randomization                                      |                      | X                      |               |               |               |
| Intervention                                |                      |                        |               |               |               |
| Cinnamon 1000 mg / Placebo                         |                      | X                      | X             | X             |               |
| Assessments                                 |                      |                        |               |               |               |
| Medical history                                    | X                    |                        |               |               |               |
| Anthropometric measurements                        | X                    | X                      | X             | X             | X             |
| SBP, DBP and pulse                                 | X                    | X                      | X             | X             | X             |
| FBS                                                | X                    |                        |               |               | X             |
| Hba1c                                              | X                    |                        |               |               | X             |
| Lipid Profile                          | X                    |                        |               |               | X             |
| Liver Profile                          | X                    |                        |               |               | X             |
| Renal Profile                          | X                    |                        |               |               | X             |
| Pregnancy Test & Contraception Review  | X                    | X                      | X             | X             |               |
| Dispense study medication                          |                      | X                      | X             | X             |               |
| Check drug compliance                              |                      |                        | X             | X             | X             |
| Check AE, SAE                                      |                      |                        | X             | X             | X             |
| Complete concomitant medications                   |                      | X                      | X             | X             | X             |

 Total cholesterol, HDL, LDL, triglycerides;  AST, ALT, AP;  Serum creatinine, ACR, eGFR, electrolytes-Na, K Cl

 Pregnancy test at screening and ongoing review of contraception adherence applies to all women of child-bearing potential. If there is concern of pregnancy, test will be repeated

## 4.8 Discontinuation criteria

A subject can be discontinued from the study due to one or more of following reasons.

- Subject's demand to discontinue the study
- Serious adverse events (SAEs) or unusual changes in clinical test results

- Principal investigator's decision to terminate the study (low rates of compliance, complications or inability to tolerate the study for various reasons)

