### 4.3 Outcome measurement

Outcomes of the study will be assessed at the end of the 3 months of the study. Anthropometric measures, SBP, DBP, FBS, serum lipids, serum creatinine, eGFR, albumin creatinine ratio (ACR) and liver profile (ALT, AST, AP) will be assessed at Visit 05. Drug compliance and any reasons for withdrawal from the study will also be recorded.

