#### **Primary effectiveness measures**

- Change in LDL levels from baseline to final follow-up at three months post randomization.

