#### 4.9 End of study

End of Study is defined as when the last subject has completed 12 weeks of treatment.

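### Section 4.8 allows removal from the study, not only from the capsules, and no Visit 5 panel is stated for those removed, so three-month LDL, liver and kidney values can be avoidably missing

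*Protocol*

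**What the plan says.** Section 4.8 begins: "A subject can be discontinued from the study due to one or more of following reasons". It lists three reasons:

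- the subject's own demand;
- serious adverse events or unusual test results;
- a decision by the principal investigator, with the grounds given as "low rates of compliance, complications or inability to tolerate the study for various reasons".

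The protocol defines no separate state in which a participant stops the capsules but stays in follow-up.

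The primary measure in section 4.3 is "Change in LDL levels from baseline to final follow-up at three months post randomization". On laboratory work, section 4.6.2 says: "During visit 05, all the laboratory investigations carried out at the visit 1 will be repeated". Table 1 agrees: lipid, liver and renal profiles, FBS and HbA1c are marked at Visits 1 and 5 only. Section 4.6.2 also says: "All participants will be requested to visit the clinic in one-month intervals for next three months".

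For people who leave, section 4.3 says: "Drug compliance and any reasons for withdrawal from the study will also be recorded". Section 4.4.3 has a participant with a positive pregnancy test complete an EOS form and be terminated, and mentions no blood panel. Section 6.3 requires adverse events to be followed until they resolve. Section 8.2 and the synopsis commit to intention-to-treat.

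**The concern.** Poor compliance, poor tolerance and adverse events are reasons to change or stop treatment. Section 4.8 makes them reasons to leave the study. An intention-to-treat comparison needs the three-month value of everyone randomised, whether or not they kept taking capsules, so a rule that ends participation for these reasons works against it.

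The schedule makes this matter more than usual. There is one LDL value after baseline, at Day 90, and no interim value to fall back on. The same holds for the liver and kidney panels, which serve a secondary safety objective.

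Those removed for compliance or tolerance are not a random sample, and their number may differ between arms. Section 1.3 mentions dyspeptic symptoms in the earlier phase I study of cinnamon, and section 4.4.2 foresees intolerance. If no sample is taken, any analysis must rest on an untestable assumption about these values. For participants who still consent, the loss comes from the rule and could be avoided.

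**Working it through.** **1. What is measured after baseline, and when**

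| Outcome | Visits 3 and 4 | Visit 5 | If removed before Day 90 |
|---|---|---|---|
| LDL and other lipids | none | yes | no value stated to be collected |
| Liver and renal panels, FBS, HbA1c | none | yes | no value stated to be collected |
| Blood pressure, anthropometry | yes | yes | earlier values may exist |
| Adverse events | yes | yes | followed until resolved (4.4.4, 6.3) |

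The gap is therefore confined to laboratory outcomes. Removal because of an unusual test result is a minor route, since no laboratory panel is scheduled between Visits 1 and 5.

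**2. The plan's own sample size (8.1)**

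Inputs: difference 10 mg/dL and SD 40 (both for total cholesterol), correlation 0.9, two-sided 0.05, 90% power.

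N = 4 × 40² × (1 − 0.9²) × (1.960 + 1.282)² / 10² = 127.8 in total, or 63.9 per group. The stated 64 per group is reproduced. With 15% dropout, 75 × 0.85 = 63.75, so 75 per arm is essentially what is needed.

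**3. Power is not the problem**

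On the same inputs, power is 94.0% if all 75 per arm have a three-month value and 89.9% if 15% do not. Dropout has been allowed for. What remains is bias.

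**4. Illustration of the bias**

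Assumptions, none of them given by the protocol:

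- k of the 75 active participants are removed and unsampled. The range is 0 to 11, because 15% of 75 is 11.25.
- Sampled active participants show 10 mg/dL.
- Unsampled active participants keep a fraction f of that effect.
- Unsampled placebo participants resemble the other placebo participants.

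Effect in all randomised = 10 × [(75 − k) + f × k] / 75. Overstatement = 10 / (that effect) − 1.

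| k | f = 0: effect (mg/dL) | overstatement | f = 0.5: effect (mg/dL) | overstatement |
|---|---|---|---|---|
| 0 | 10.00 | 0% | 10.00 | 0% |
| 3 | 9.60 | 4.2% | 9.80 | 2.0% |
| 6 | 9.20 | 8.7% | 9.60 | 4.2% |
| 11 | 8.53 | 17.2% | 9.27 | 7.9% |

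If the unsampled keep the full effect (f = 1), there is no overstatement at any k.

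**5. Scale against sampling error**

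SE with 64 per arm = √(2 × 40² × 0.19 / 64) = √9.5 = 3.08 mg/dL. The largest gap is 10 − 8.53 = 1.47 mg/dL, and 1.47 / 3.08 = 0.48 SE.

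**6. Liver and kidney panels**

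For k = 3, 6 or 11, the share of an arm with no final value is 3/75 = 4.0%, 6/75 = 8.0% or 11/75 = 14.7%. These are logical bounds, not expected rates.

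**The case against.** The strongest reply is that the protocol is silent on sampling after discontinuation and does not forbid it. Section 4.6.2 asks all participants to attend monthly, the primary measure is fixed at three months from randomisation and not at the end of treatment, section 8.2 promises intention-to-treat, and 4.8 is permissive. Visit 5 carries the EOS label and includes blood collection, so completing an EOS form at early exit might imply the panel. The form itself is not shown.

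Part of this stands. A reader might infer that 4.8 bars a later draw, and it does not. But someone discontinued from the study is, on the plain meaning, no longer on its visit schedule. The request in 4.6.2 describes the ordinary course and does not say it continues after removal. The one termination the protocol spells out, for pregnancy, gives a form and no panel.

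Other limits also stand:

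- The serious-adverse-event item is a separate entry in 4.8 and is not tied to the investigator's decision.
- Investigators are blinded (4.4.2, 4.5), so removal cannot knowingly follow allocation, although tolerance itself can still differ by arm.
- Section 4.4.2 allows dosing after meals for intolerance, which should prevent some removals.
- Reported adverse events are followed until resolved, so clinically apparent liver or kidney events are not dropped. What is lost is the scheduled panel.

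A reader might also cite section 4.9, "End of Study is defined as when the last subject has completed 12 weeks of treatment", as further evidence that stopping treatment ends follow-up. That sentence defines the end of the whole trial and says nothing about an individual who stops capsules.

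Finally, it may be said that missing data belong in the statistical analysis plan. How they are analysed may. Whether a participant is sampled at Day 90 is trial conduct, and no analysis plan can recover a sample that was never taken.

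**Conclusion.** The point holds as a weakness in the discontinuation rule that should be fixed. As worded, 4.8 can remove consenting participants for treatment-related reasons, and no provision secures their only post-baseline LDL, liver and kidney values. This undercuts the intention-to-treat commitment without contradicting it outright.

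The size cannot be derived from the protocol, which does not split the 15% dropout by cause. A reader might take the 17% overstatement, or the 14.7% without final safety panels, as the expected effect. Neither is supported. Both need every anticipated dropout to be a removal under 4.8 with no sample and none to leave at their own request, and the 17% also needs no retained effect in those removed. The 10 mg/dL and SD 40 are total-cholesterol figures used here for LDL only as an illustration. Even on those terms the gap is about 1.5 mg/dL, or half a standard error. With three unsampled it is 0.2 to 0.4 mg/dL.

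**What to change.** In section 4.8, state that stopping the capsules for any reason other than withdrawal of consent does not end study participation, and that these participants are asked to attend Visit 5 at Day 90(+5) for the scheduled fasting blood and urine panel. Leave the pregnancy termination rule in 4.4.3 unchanged. Add a matching line to 4.4.4 and a footnote to Table 1.

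Optionally, offer a participant who says they will not return the same fasting panel once, at or soon after discontinuation. It would serve mainly liver and kidney safety, and should be flagged as not being a three-month LDL value.

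The cost is the effort of bringing back a few participants per arm (0 to about 11 on the assumption above) for a draw that completers already have, plus a minor amendment with the notification, and re-consent if required, set out in section 13. Nothing is added for completers.

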#### 4.9 End of study

End of Study is defined as when the last subject has completed 12 weeks of treatment.

#### 4.10 Termination of the entire trial

Premature termination of the clinical trial will be considered if the principal investigator believes it is necessary to terminate the clinical trial for safety reasons, or when the clinical trial proves to be impracticable.

## 5. INVESTIGATIONAL MEDICINAL PRODUCT

The treatment drug is SaaraLife OptiHeart - Ceylon Cinnamon extract capsule. It is a capsule containing a standardized *C. zeylanicum* bark extract as the active ingredient.

### 5.1 Formulation

The raw material (cinnamon bark) used in the production had been authenticated by the Industrial Technology Institute, Sri Lanka (ITI; Report No: CTS1715632). Fresh powdered cinnamon feed with particle size distribution ranging from 250  $\mu\text{m}$  to 1 mm is fed to the extractor. Extraction is carried out multiple times with aqueous + ethanol solvent to ensure the recovery of the maximum content of active compounds. Once water and ethanol solvent are evaporated mixture is passed through an ethanol recovery unit for recovery of ethanol. Then the concentrated output is passed through a vacuum dryer at specific temperatures to obtain a powder (with minimum of 15% proanthocyanidins (PAC A). Finally, 500mg of this powder is packed into size 0 capsules. The capsule preparation was carried out at a manufacturing site with GMP (Good Manufacturing Practices) certification.

The placebo capsule will contain pharmaceutical grade wheat flour (tasteless, odourless white colour fine powder). The placebo oral capsule will be identical in shape, size, weight and texture to the *C. zeylanicum* oral capsule. In order to mask the aroma, cinnamon quills would be put into packets containing both the placebo and cinnamon capsules.

### 5.2 Packaging and Labelling

Labels will include: (a) name of the sponsor; (b) pharmaceutical dosage, route of administration, quantity of dosage units (and name/identifier of the product and strength/potency); (c) the code number to identify the contents and packaging operation; (d) the trial subject identification number, where applicable; (e) directions for use; (f) “for clinical trial use only”; (i) the storage conditions;

### 5.3 Storage and Handling

Cinnamon capsules should be stored at controlled room temperature below 25°C (77°F). Storage conditions are specified on the label. Until dispensed to the subjects, all bottles of study drugs should be stored in a securely locked area, accessible only to authorized site personnel.

To ensure the stability and proper identification, study drugs should not be stored in a container other than the container in which they were supplied. Consideration should be given to handling, preparation, and disposal through measures that minimize drug contact with the body.

### 5.4 Accountability for Study Drug

In accordance with GCP, the clinical unit will account for all study medication. The clinical unit are responsible for study medication accountability, reconciliation, and record maintenance.

Drug accountability records will be maintained during the study as follows:

- Amount of study medication received from the Sponsor
- Amount distributed to each patient and returned by them
- Amount of unused drug returned to the Sponsor or destroyed at Sponsors request

In addition, in the event of necessary disposal of opened but wasted medication, the disposal should be documented appropriately (i.e. witnessed), in accordance with applicable local regulations, and GCP procedures.

Participants are required to return used and unused bottles to the clinical unit. Storage bags will be provided to each patient. For all unused study medication, the patient should adhere to the storage instructions until the study medication is returned to the clinical unit.

### 5.5 Investigational Medicinal Product Return or Disposal

Following accountability of study medication at the study site and on authorization of Coordinating Center, study medication will be returned to originator for destruction.

## 6. SAFETY ASSESSMENT

### 6.1 Definitions of Adverse Events, Adverse Reactions, and Serious Adverse Events

|                       |                                                                                                                                                                                                                                                                                                                                                                                                                                                                                                                                                                                                           |
|-----------------------|-----------------------------------------------------------------------------------------------------------------------------------------------------------------------------------------------------------------------------------------------------------------------------------------------------------------------------------------------------------------------------------------------------------------------------------------------------------------------------------------------------------------------------------------------------------------------------------------------------------|
| AE                    | Any untoward medical occurrence in a participant to whom a medicinal product has been administered, including occurrences which are not necessarily caused by or related to that product.                                                                                                                                                                                                                                                                                                                                                                                                                 |
| Adverse Reaction (AR) | 
An untoward and unintended response in a participant to an investigational medicinal product which is related to any dose administered to that participant.
 
The phrase "response to an investigational medicinal product" means that a causal relationship between a trial medication and an AE is at least a reasonable possibility, i.e. the relationship cannot be ruled out.
 
All cases judged by either the reporting medically qualified professional or the Sponsor as having a reasonable suspected causal relationship to the trial medication qualify as adverse reactions.
 |
| SAE                   | 
A SAE is any untoward medical occurrence that:
 

• results in death

• is life-threatening

• requires inpatient hospitalisation or prolongation of existing hospitalisation

• results in persistent or significant disability/incapacity

• consists of a congenital anomaly or birth defect*.

 
Other 'important medical events' may also be considered a SAE when, based upon appropriate medical judgement, the event may
                                                                                      |

|                                                       |                                                                                                                                                                                                                                                                                                                                                                                                                                                                                                                           |
|-------------------------------------------------------|---------------------------------------------------------------------------------------------------------------------------------------------------------------------------------------------------------------------------------------------------------------------------------------------------------------------------------------------------------------------------------------------------------------------------------------------------------------------------------------------------------------------------|
|                                                       | jeopardise the participant and may require medical or surgical intervention to prevent one of the outcomes listed above.                                                                                                                                                                                                                                                                                                                                                                                                  |
| Serious Adverse Reaction (SAR)                        | An AR that is both serious and, in the opinion of the reporting Investigator, believed with reasonable probability to be due to one of the trial treatments, based on the information provided.                                                                                                                                                                                                                                                                                                                           |
| Suspected Unexpected Serious Adverse Reaction (SUSAR) | 
A serious adverse reaction, the nature and severity of which is not consistent with the Reference Safety Information for the medicinal product in question set out:
 
 
• in the case of a product with a marketing authorisation, in the approved summary of product characteristics (SmPC) for that product
 
• in the case of any other investigational medicinal product, in the approved investigator's brochure (IB) relating to the trial in question.
 
 |

